### Quality control

This study will use a randomized control design, and the randomization protocol will be held by the management team of the study team who do not participate in the project to ensure random allocation and control biases.This study is limited to the inclusion criteria and will establish a clear inclusion and exclusion criteria to control biases.This study will use blind method evaluation and will evaluate the efficacy and safety by evaluators who do not know the grouping situation to ensure the reliability of the research results.During the study, the pain tester, muscle strength, and joint mobility test will be carried out according to various standard operating procedures to control biases.The quality control inspection of this study will be conducted by the researcher to designate at least one non-quality implementer to conduct a quality check on the research of each center of the subject to control the bias.

### Quality assurance

Initial meeting of the project will be held to conduct unified training. Key training will be carried out on the project implementation plan and SOP, so that each participant will master the research process and specific implementation rules to ensure the reliability of the conclusion. During the study, each center will be supervised regularly to control biases.

### Data collection and management

Paper CRFs will be used to record all the information required from the protocol which will be collected from the hospital. There will be an instructions page at the start of each postal questionnaire and for the more complex hospital CRFs. Each trial participant will have a unique identification number that will be pre-recorded on all CRFs. Initially, the data will be listed on the CRF form, and after interviewing 20 participants, the data of clinical research will be input in a group of 20 cases. Besides, the input approach will be double-input, which will be input by two data input personnel without contact. Meanwhile, the data manager will compare the differences with the initial data and fill in the reasons for it. During the trial, a monthly data inspection will be needed, and the content involves data assembled by every center abnormal data, and delayed data in progress tracking. The data input in the paper type of CRF form will be received from the primary data. Furthermore, the researcher will preserve the copies of the test-related data, the data of the subject, and all other initial data until the announcement from the team leader to discard them. Moreover, researchers at the center should obey the rule of confidentiality of the trial. After the primary data which will be held for 3 years, non-research team members cannot browse and borrow it.

### Data monitoring and auditing

As this test is a multi-center study, therefore, before the start of each research center, the team leader from every unit will monitor the research center. They will check whether the research-related facilities and equipment are complete and well prepared, and whether or not the researchers are proficient in the test operation process and equipment use. The chief investigator of the team leader unit will inform each clinical center investigator of their responsibilities, and how to correctly and completely fill in the relevant documents for the trial. Through the investigator training session, the investigator and his team will understand the trial plan, completing the CRF form, use of the evaluation tools, as well as the test procedures. Then the chief investigator of the team leader unit will visit the start-up status of each center. During the test, the third-party data management staff will regularly and strictly monitor the filling of the CRF form. The third-party data management staff will mainly monitor whether the researcher screens the subjects in accordance with the admission criteria. During the inspection, the CRF form will be checked if it is accurate, directly with reference to the original data.

### Informed consent

Before conducting a conversation with the subject, the researcher should understand and check whether the informed consent is comprehensive, whether it meets the ethical requirements, and whether it meets the rights and obligations of the subjects as specified in the “Helsinki Declaration.”Explain the entire contents of the informed consent form to the subject in a simple and understandable language. The subject will voluntarily participate in the clinical trial and has the right to withdraw at any stage of the trial without discrimination and retaliation. The personal data and information of the participants participating in the trial will be kept confidential, and subjects may be assigned to different trial groups to take different treatments. Informed consent should be signed by the subject or other legal representative.

### Patient dropouts

Investigators will have the authority to terminate patient participation at any time if the investigator deems it is in the best interests of the patient. Termination criteria are as follows: (1) Patients with serious adverse reactions or combined with other critical illnesses in the study. (2) The subject asks to withdraw from the trial during the course of treatment and persuasion is ineffective. (3) Subjects who are not cooperating to the treatment and persuasion are ineffective by the doctor. (4) If the subject receives half of the treatment, then he or she should be included in the statistical analysis of efficacy.

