
### Rationale for the trial design

Currently, few studies report on the comparative effectiveness of using stuck-moving needle acupuncture MTrp for idiopathic frozen shoulder. However, clinical studies have reported the benefits of acupuncture [26], but lack the comparison and the effect of different methods. Thus, in this study, we designed a prospective randomized controlled trial to determine the clinical effectiveness of stuck-moving needle acupuncture MTrp and common acupuncture in reducing idiopathic frozen shoulder. Further, we compared them to physical exercise programs. Although the double-blind, placebo-controlled trial is the golden standard to assess a therapeutic effect, however, this method is difficult to use for manipulation technique of sham needling. With a needle stimulation, the process of manipulation for stuck-moving needle acupuncture MTrp and common acupuncture is easily distinguished. Thus, in this study, we have not included blinding and placebo. However, this project uses a blind method for evaluation. Efficacy assessments were performed by third parties, and they were unaware of the grouping situation. In addition to the outcome measurement choice, this study will also evaluate additional patient satisfaction and short form-36 questionnaire (SF-36), and the safety evaluation.

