### Blind method

This study will use the blind method for evaluation. Efficacy assessments will be performed by third parties who do not know the grouping situation. Further, all participants in the assessment will receive uniform training. Blind statistical analysis will be used in the data summary stage, that is, statistical analysts will be unaware of the grouping situation and content. Randomized staff, study researchers, operators, and statisticians will be kept unaware of the experiment blinded to ensure that subjects, evaluators, and statisticians do not understand the grouping situation.

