### Statistical analysis

All statistical analysis will be carried out by the professionals using SPSS (v21.0) software. The participants in the statistical analysis will be unaware as well for the specific grouping content of the trial. This study will use a full analysis set (FAS) and per protocol set (PPS), and the final conclusion will be based on FAS. The full analysis set (FAS) is based on the intent to treatment (ITT). Patients who participate in randomization and receive at least one treatment will be included in the analysis. In the FAS analysis, for patients who do not complete the trial, the main indicators of the missing will be derived from the Last Observation Carried Forward (LOCF). Continuous variables will be presented as mean ± standard deviation (normally distributed data) or medians and ranges (non-normally distributed data). Frequencies and percentages will be used to count the data. All statistics will be performed by bilateral differential test, with *P* value < 0.05 considered statistically significant.

For the balance of basic values, analysis of variance or chi-square test or rank sum test will be used. For the primary and secondary outcome, the analysis of variance will be used. If confounding factors have an impact on the results, then the co-variance analysis will be used. For the safety analysis, the incidence of three groups of adverse events will be compared using a chi-square test, and the adverse events that will occur in this trial will be listed. At the same time, the paired *t* test will be used to compare the differences between the groups before and after treatment. The comparison among the three groups before and after treatment will be analyzed by variance. The rate changes before and after treatment in the three groups will be measured by chi-square test or non-parametric test.

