The setting of control group also plays an important role in the efficacy evaluation. It is the basis of accurate evaluation of curative effect. According to the WHO published guidelines for clinical research in acupuncture and moxibustion requirements for the establishment of control groups in clinical studies of acupuncture and moxibustion, we set up two control groups. Exercise programs are the basic treatment and also a control group. The common acupuncture group is a positive control group, and the stuck-moving needle was used to acupuncture MTrp as the treatment group, to verify the effectiveness of treatment group.

The selection of appropriate outcome is crucial when designing clinical trials. A review of shoulder pain trials found that trialists reported pain in 87%, function in 72%, range of motion in 67%, adverse events in 27%, patient-reported treatment success in 24%, strength in 18%, and health-related quality of life in 18% [37]. Therefore, we choose primary outcomes including a measure of pain (VAS) and range of motion (ROM), whereas secondary outcome included a measure of pain (PTT and PPT), function (OSS), health-related quality of life (SF-36), patient satisfaction evaluation, and adverse events. The measurement time was from baseline through the 12-week follow-up period.

However, this study also has its limitation. First, the implementation of the blind method is difficult due to the nature of acupuncture, and the masking of acupuncturists is quite difficult to achieve. However, the statistician will be masked. Second, the follow-up time is too short, probably due to the current status of research funding and research time, and patients were followed up for a period of 12 weeks after the end of treatment in this study. Follow-up was performed at week 4 and week 12. Frozen shoulder is a chronic degenerative osteoarthropathy with a long course and the high possibility of recurrence. Therefore, for the future trial design, the follow-up time should be appropriately extended and comprehensive evaluation should be carried out with the long-term treatment effect for frozen shoulder by the stagnant acupuncture method. Nonetheless, the trials carried out in this study and subsequent results will provide more reliable evidence for clinical treatment of FS.

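### The dropout rule recognises a request to withdraw only during treatment and only after persuasion has failed, contrary to the unconditional right stated under Informed consent

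*Protocol article*

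**What the plan says.** Two neighbouring sections of the Protocol article deal with leaving the trial.

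- **Informed consent** states that participation is voluntary and that the subject "has the right to withdraw at any stage of the trial without discrimination and retaliation". No condition is attached.
- **Patient dropouts** opens with the investigator's own power: "Investigators will have the authority to terminate patient participation at any time if the investigator deems it is in the best interests of the patient". It then lists termination criteria. The second is "2) The subject asks to withdraw from the trial during the course of treatment and persuasion is ineffective". The third, which concerns non-cooperation, repeats the persuasion test: "3) Subjects who are not cooperating to the treatment and persuasion are ineffective by the doctor".

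Three other parts of the document bear on the consequences.

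- **Who knows the arm.** Rationale for the trial design says "Thus, in this study, we have not included blinding and placebo", apart from blinded evaluation. The Discussion concedes that "the masking of acupuncturists is quite difficult to achieve". Blind method says the opposite of treating staff: "Randomized staff, study researchers, operators, and statisticians will be kept unaware of the experiment blinded".
- **Who is analysed.** Statistical analysis bases the final conclusion on the full analysis set (FAS): "Patients who participate in randomization and receive at least one treatment will be included in the analysis". Missing values of the main indicators in non-completers are filled by last observation carried forward (LOCF), and a per-protocol set is also analysed.
- **Who assesses.** Outcomes assigns assessment to independent, trained assessors who are unaware of group.

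**The concern.** A patient who signs the consent form is told that leaving is possible at any point. Staff who follow the dropout section are told something narrower: a request counts once persuasion has been tried and has failed, and the section speaks only of requests made during treatment. Patients are promised one thing while staff are instructed in another. The person most affected is the patient who finds the treatment hard to tolerate and asks to stop. By the protocol's own account, stuck-moving needling is the stronger stimulus, and patients may report pain while it is applied.

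The primary issue is therefore voluntary participation. The secondary issue is statistical. If persuasion is applied with different energy in different arms, the dropout pattern partly reflects staff effort and not only how patients fared. That matters for reading dropout as a sign of tolerability, and for how many primary outcome values are observed and how many are carried forward.

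**Working it through.** The plan states no figure on this point, so there is nothing to reproduce. The check is a comparison of the text.

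1. **Condition on the request.** Informed consent attaches none. Patient dropouts, item (2), joins the request to failed persuasion with an *and*. Read literally, a request alone does not meet the criterion. Item (3) uses the same construction, so the phrase is not an isolated slip.

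2. **Timing of the request.** Informed consent covers every stage. Item (2) covers the course of treatment. Study design gives 3 weeks of treatment and 12 weeks of follow-up, so the two statements do not cover the same period.

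3. **Can staff refuse?** No. Under item (2) a patient who maintains the request meets the criterion and leaves. Staff can influence retention but cannot block withdrawal.

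4. **Do those who persuade know the arm?** Item (2) names no persuader. Item (3) names the doctor, but for non-cooperation. Blind method claims that researchers and operators are unaware. That claim is hard to accept for anyone delivering treatment. The three arms are trigger-point needling with a twisted and lifted needle, acupoint needling with the needle retained for 30 minutes, and exercise without needles. Rationale for the trial design and the Discussion both accept that treatment cannot be masked. Knowledge of the arm is therefore very likely for treating staff, but it is an inference and not something the document states about whoever handles withdrawal requests.

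5. **How could retention reach the result?** It does not decide FAS membership, which needs only randomisation and one treatment. Three routes remain.
   - *Values inside the FAS.* Outcomes places the first post-baseline assessment at the end of treatment. A patient who leaves during treatment and is not assessed has only the baseline value to carry forward, which is a change of zero. The same patient, if persuaded to stay, contributes an observed change.
   - *The per-protocol set*, if its membership depends on completing treatment.
   - *Patient dropouts, item (4)*, which brings patients who received half the treatment into the efficacy analysis. This rule differs from the FAS definition.

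6. **Size.** The effect would depend on how many patients in each arm ask to leave, how many are persuaded, and how they would have fared. The document gives none of these. Any number would rest on an invented count, so none is given.

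**The case against.** The strongest reply is that the dropout list is loosely drafted and was never meant as a complete code. It starts from the investigator's authority, its item (4) is an analysis rule and not a termination criterion, and Informed consent already covers withdrawal at any stage. On that view the contradiction is one of wording. This is fair as far as it goes. It does not remove the problem, because staff who apply the dropout section as written would still try persuasion before accepting a request.

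The same reply disposes of several stronger readings that a reader might infer and that the documents do not support:

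- **That staff decide who is retained.** They do not, because an unpersuaded patient leaves.
- **That 12 of the 15 weeks after randomisation have no way out.** This overreads the list, since Informed consent supplies the right for that period.
- **That the protocol puts arm-aware staff in charge of withdrawal.** No persuader is named in item (2), and Blind method says the contrary, implausible as that is for operators.
- **That persuaded patients report pain to the people who pressed them to stay.** Assessment is assigned to independent assessors unaware of group. The description of the VAS has a physician record the score, but nothing identifies that physician as a persuader.
- **That the primary comparison is shown to be biased.** FAS membership does not depend on retention, and the remaining routes cannot be sized.
- **That failing to record withdrawal reasons is an error.** A condensed article may leave this to the full protocol or case report form.

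**Conclusion.** The contradiction stands. Informed consent gives an unconditional right to withdraw at any stage, while Patient dropouts, item (2), recognises a request only within treatment and only once persuasion has failed. The two must be reconciled. This conclusion rests on the wording alone and needs no assumption.

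The statistical consequence is possible but not established. It assumes that those who persuade know the arm, which is very likely for treating staff, and that they persuade unequally, which is unknown. If both hold, dropout and the share of LOCF-filled values could differ between arms. The documents do not allow this to be sized, so it supports the change without being the main reason for it. The point is worth acting on because the change protects participants and costs very little.

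**What to change.** Align Patient dropouts, item (2), with Informed consent: remove the persuasion condition and the restriction to the treatment period, so that a request to withdraw is honoured whenever it is made.

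Recording the stated reason for each withdrawal, and reporting withdrawals by arm and reason, would be a useful optional addition. It would let readers judge whether dropout differs between arms. It does not correct an error in the plan.

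The cost is one sentence of protocol text and, if the option is taken up, one case report form item. Trial status dates the first enrolment to 02 Jan. 2020, so the change would be made with the trial under way. Protocol amendments requires important modifications to be communicated to the fund regulator, participants, registries and journals. The other downside is possibly a few more recorded withdrawals.

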### Rationale for the use of intervention

Idiopathic frozen shoulder treatment methods are generally divided into three types: operative treatment, conservative management, and minimally invasive treatment [13]. The operative treatment includes arthroscopic capsular release and manipulation under anesthesia, while conservative management includes exercise therapy, superficial heat or cold, electrotherapy, and medication. Minimally invasive treatment includes acupuncture and injections [9, 13]. Recent numerous studies have focused on acupuncture treatments for idiopathic frozen shoulder, as it is safer than medical treatments and has fewer side effects, specifically to remedy for chronic shoulder pains [14, 15]. Based on previous studies, it has been suggested that the strong stimulation of acupuncture may enhance the effects of pain relief by triggering “diffuse noxious inhibitory controls” and may increase the secretion of endorphins by stimulating internal activity of the central nervous system [16, 17]. In addition, acupuncture can inhibit the inflammatory response of the local shoulder joint [18]. However, the acupuncture site, manipulation, and intensity of the stimulation affect the efficacy of acupuncture therapy [19]. The common acupuncture stimulates the acupoints with filiform needles. It is easy to operate and the patient suffers less pain, whereas stuck-moving needle therapy is different from common acupuncture in the needle instrument, manipulation, and stimulation site [20]. Stuck-moving needle applicator applies active motion to the stuck needles fixed at the myofascial trigger points to achieve a benign, suitable, and effective needle volume, eventually to get acupuncture effect. Consequently, stuck-moving needle therapy has higher requirement on the operator and has stronger acupuncture stimulation compared with common acupuncture. The myofascial trigger points (MTrp) have often been used in the treatment of myofascial pain syndrome. Acupuncture is a type of myofascial trigger point therapy which provides immediate relief of pain related with myofascial trigger point [21–23]. Moreover, results from a few studies suggested that the response to trigger points is greater than the response to treating traditional acupoints [24, 25]. These results suggest that the stuck-moving needle stimulation of myofascial trigger points might be effective for patients with idiopathic frozen shoulder. Our pilot study showed that stuck-moving needle was used to acupuncture myofascial trigger point and was effective in improving the pain and movement limitation of the patients with idiopathic frozen shoulder. Physical exercise programs are widely used to resolve the shoulder joint pain which ultimately limits the frozen shoulder, and considered as the effective basic therapy [14] which is also supported by clinical evidences [13]. This information permits the use of physical exercise programs as the basic therapy for a control treatment. The present study was carried out to compare the effectiveness of stuck-moving needle acupuncture Trp and common acupuncture practices.

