## Intervention

Participants will be randomly allocated into one of three groups: A, the stuck-moving needling acupuncture MTrp group; B, the common acupuncture group; and C, the physical exercise group as the control group and the basic therapy for groups A and B. Three acupuncturists with at least 5 years of clinical experience in acupuncture practice will be recruited from Chinese Medicine Practitioners, and only these acupuncturists will be allowed to perform all acupuncture sessions. Several training sessions will be carried out prior to the commencement of the study which will ensure consistency in the skills of the acupuncturist. During the 3-week treatment period, patients will receive nine sessions of acupuncture (3 weekly cycles of one treatment every other day, followed by a 1-day break). One-time stuck-moving needles (0.40 mm × 40 mm/0.40 × 25 mm, the patent of Li Zhenquan produced, Beijing, China) and one-time acupuncture sterile needles (0.25 mm × 40 mm/0.25 × 25 mm, Hwato, Suzhou, China) will be used in the trial. All acupuncture treatments will be provided for free to improve adherence to the intervention protocol. Patient and acupuncturist signatures will be required after each acupuncture session to monitor adherence. Other treatments that may affect the effect indicators of this study will be prohibited, including oral painkillers for nearly 3 months and physical therapy such as acupuncture and massage.

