### Group C: physical exercise control group

The physical exercise method of the shoulder joint is carried out according to the physical exercise program recommended in the Evidence-based clinical guidelines for the diagnosis, “The Assessment and Physiotherapy Management of Contracted (frozen) Shoulder” prepared by Hanchard et al. [13] in 2012. The patient’s training will be consisted of 12 sports units, including active and passive training, for a total of 50 min. Each workout will have a professional physiotherapist ([name] physical therapist) to guide the treatment and provide a practical exercise program for the patient. Treatment will take place 3 times a week for 3 weeks for a total of 9 treatments. The basic movements are as follows: active shoulder joint exercise with bare hands, let the patient use the diseased shoulder joint as the axis of shoulder joint movement, and do small rotation movements of the shoulder joint. First, rotate clockwise for 4 min, then counterclockwise for 4 min. Subsequently, the intensity can be increased; the two movements alternated for a total of 20 min. In the later stage, strength of exercise will be increased with the help of the physiotherapist, and the passive movement will be carried out for 10 min. Then, it will be used for shoulder flexion, abduction, extension and internal rotation, external rotation, and other actions by means of assistive devices such as shoulder rotation training device and fitness ball technique. Finally, the standing training exercises will be carried out for the spine and side bends of the spine.

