### Adverse events

All adverse events that will occur during the study will be recorded. The records will include the description of these events, start time, severity and frequency of occurrence, end time, ongoing treatment, results, and the track and analysis.
A serious adverse event (SAE) is an adverse event in which any of the following circumstances can occur.
An event that causes the patient to die or endanger the patient’s life.The events that result in permanent or significant disability or loss of function in the patient.The events that lead to hospitalization.The important medical events need to use drugs or surgery to prevent serious consequences.Treatment of serious adverse events

Once a serious adverse event is found, the study physician must report to the study leader and the study team. The study team should report to the Ethics Committee and the responsible units within 24 h and record the serious adverse events in the original data. Original data may include carefully filling out the adverse event report form, recording the start time, the severity, the final outcome, the relationship with acupuncture treatment, the details of the treatment, and should immediately consult the relevant departments to take the necessary treatment.

The trial of a SAE patient will be discontinued and become a withdraw subject, while all costs for handling adverse events will be covered by this study.

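### Two treatment-received thresholds, at least one session and half of the sessions, govern entry to the efficacy analysis, and neither amounts to analysing all randomised patients

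*Protocol article*

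**What the plan says.** The Statistical analysis section names two sets, a FAS and a per protocol set (PPS), and ranks them: "the final conclusion will be based on FAS". On the nature of the FAS it says "The full analysis set (FAS) is based on the intent to treatment (ITT"), and its entry rule is "Patients who participate in randomization and receive at least one treatment will be included in the analysis". Missing main outcomes of non-completers are filled by last observation carried forward (LOCF). The PPS is named without an entry rule.

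The Patient dropouts section lists reasons for ending a patient's participation, among them serious adverse reactions and persistent non-cooperation with treatment. Its item (4) then reads "If the subject receives half of the treatment, then he or she should be included in the statistical analysis of efficacy". It does not mention the PPS.

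The Adverse events section adds: "The trial of a SAE patient will be discontinued and become a withdraw subject".

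The treatment course is the same length in every arm. In the acupuncture arms "patients will receive nine sessions of acupuncture" (Intervention), and the exercise programme runs "for a total of 9 treatments" (Group C).

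**The concern.** The set that carries the primary conclusion should be defined once, and membership should not depend on what happens after randomisation. Here there are two thresholds, both counted in treatment received.

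This matters more because allocation is hard to hide. Rationale for the trial design says that treatment is not blinded and that the two needling methods are easily told apart. The Discussion lists blinding as a limitation, and a patient given exercise alone will know it. Blind method says instead that subjects are unaware of their group, and that statement needs to be reconciled with the others.

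If patients can recognise their arm, declining treatment or stopping early may depend on it. The protocol gives a reason to expect this: the stuck-moving needle "has stronger acupuncture stimulation compared with common acupuncture", and the same section describes common acupuncture as less painful for the patient. If poorly responding or poorly tolerating patients leave one arm more often and are then excluded, that arm looks better than it is.

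A related problem is that patients who stop treatment for certain reasons are also taken out of the trial, and no section says that their outcomes are still measured.

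**Working it through.** **1. The two rules side by side.** Both regimens have 9 sessions, and 9 / 2 = 4.5.

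| Sessions received | FAS rule (at least one) | Item (4) (half) |
|---|---|---|
| 0 | out | threshold not met |
| 1 to 4 | in | threshold not met |
| 5 to 9 | in | in |

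The rules differ for patients with 1 to 4 sessions. A randomised patient with no session is outside the FAS, so the FAS is a modified ITT set.

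**2. What item (4) does.** It is an if-then inclusion statement. If every patient with at least one session is already in the efficacy analysis, the statement adds nobody. It has an effect only if dropouts below half are left out, and that is the conflict with the FAS rule.

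**3. What happens to outcomes after stopping.** The Outcomes section gives four assessments: baseline, end of treatment, week 4 of follow-up and end of follow-up (week 12). The first post-baseline value is therefore at the end of treatment. A patient withdrawn after 1 to 4 sessions and not assessed afterwards has only a baseline value. If LOCF carries that forward, the recorded change is 0.

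**4. Scale, by illustration.** The protocol gives no figure for this effect, so there is none to reproduce. From Sample size estimation: 36 randomised per arm, with planned VAS reductions of 5.2 (stuck-moving needle, A) and 4.7 (common acupuncture, B). The planned A-B difference is 5.2 - 4.7 = 0.5.

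Assumed, not in the protocol: 4 of 36 in arm A stop before half the sessions and improve by 3.0, the other 32 average 5.2 (a gap of 2.2), and there is no such loss in arm B.

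- Mean with all 36: (32 × 5.2 + 4 × 3.0) / 36 = 178.4 / 36 = 4.96
- Mean without the four: 5.20
- Shift: 5.20 - 4.96 = 0.24, which is 0.24 / 0.5 = 49% of the planned difference

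If the four are instead kept with baseline carried forward, the mean is 32 × 5.2 / 36 = 4.62, which is 0.58 below 5.20.

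In general, shift = share excluded × gap. For an assumed upper case of 6 of 36 (16.7%) excluded from one arm:

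| Assumed gap (VAS points) | Shift in arm mean |
|---|---|
| 1 | 6/36 × 1 = 0.17 |
| 2 | 6/36 × 2 = 0.33 |
| 3 | 6/36 × 3 = 0.50 |

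**The case against.** The strongest reply is that there is no literal contradiction. Item (4) says who should be included, no sentence excludes a patient with 1 to 4 sessions, and the Statistical analysis section gives the FAS precedence with an explicit entry rule. A half-treatment threshold would also suit a PPS, whose detailed definition a journal article may leave to the full protocol. This stands in part. A reader might infer that the protocol openly excludes early stoppers, or leaves the analysis set to be chosen once data are seen. The text supports neither. What remains is that item (4) speaks of the efficacy analysis without qualification, is not tied to the PPS, and works only as an exclusion.

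A second reply is that randomised with at least one treatment is a common FAS definition, and that it drops only patients who received nothing. That is fair as to numbers, since the protocol gives no basis for estimating how many there would be. It does not answer the point that not starting can depend on a recognisable allocation.

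Third, a reader might infer that outcomes of withdrawn patients are definitely not collected. The documents say only that participation ends or that the patient becomes a withdrawn subject. The end of measurement is the natural reading, but it is an inference. Such patients with at least one session stay in the FAS, so what would be lost is observed late data, not the patient.

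Fourth, the illustration puts all the loss in one arm. The six extra patients per arm (36 - 30) allow for missing samples and loss to follow-up in general, and are no forecast of early stopping. Both criticisms are right, so the figures show scale only.

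**Conclusion.** The concern holds in this form. The FAS rule and item (4) are inconsistent for patients with 1 to 4 of nine sessions, and both condition on treatment received after an allocation that patients can in practice recognise. Some patients who stop treatment become withdrawn subjects with no statement that they are still assessed, so their week-12 values would probably be LOCF values.

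This rests on reading item (4) as a working threshold, on the unblinded description being the correct one despite Blind method, and on withdrawal ending measurement. No bias of a particular size can be claimed. Under the stated assumptions the shift in one arm's mean is about 0.24, and 0.17 to 0.50 in the upper case. That is not small beside a planned A-B difference of 0.5, but it depends entirely on dropout that is assumed and one-sided.

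**What to change.** 1. Define the primary set as all randomised patients, analysed in the arm to which they were randomised, with no condition on treatment received or on having a post-baseline value. A post-baseline condition should not be added: the first such visit is at the end of treatment, so it could drop early stoppers whom the present FAS keeps. Report by arm the number of patients without any post-baseline outcome.
2. Delete item (4) of Patient dropouts, or state that it defines the PPS only.
3. State that stopping treatment does not by itself end outcome collection. The scheduled end-of-treatment, week-4 and week-12 assessments are still sought where the patient consents and the investigator sees no reason against it. The clinical rules for stopping treatment stay as they are.
4. Reconcile Blind method with Rationale for the trial design and the Discussion on whether patients know their group.

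The cost is protocol wording and a few more already scheduled visits to pursue. The effect estimate may be slightly diluted by patients who received little or no treatment. The planned sample of 36 per arm (108 in total) does not change.
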